### Outcomes

Measurements are performed on patient and team level. A detailed description of the measures is given below and an overview of all measurements is given in Table 2. The measurements will be performed at baseline and three and twelve months after the start of the intervention. A large part of the measurements are performed routinely as part of standard care. These Routine Outcome Monitoring (ROM) screenings are implemented in all mental health care organisations in the North of the Netherlands. Trained nurses visit patients yearly after individual appointments have been made or schedules are set up by team coordinators. Results are recorded in the patient record form and discussed with the patient. When ROM screenings were first implemented, patients were asked for informed consent to use their ROM data for research purposes. Only anonimized data are used for scientific research, and the procedure was approved by the Medical Ethical Committee of the University Medical Center Groningen. For the ELIPS data collection, two regular, yearly ROM screenings will be used (baseline and 12 months follow up) and an additional ROM screening will be carried out at three months for which patients receive a small participation fee (€5,00).

**Table 2 Tab2:** **ELIPS Trial measurements overview**

		**Baseline**	**3 months**	**Monthly, during monitoring phase**	**12 months**
**Measurements on patient level**					
General information	Age, gender, birth year, diagnoses, year of first psychosis	X			
Physical measures	Height	X	X		X
	Weight	X	X		X
	Waist circumference	X	X		X
	Blood pressure (systolic, diastolic, pulse)	X	X		X
	Body fat (%)*	X	X		X
Lab test	Lipids (Total cholesterol, LDL-cholesterol, HDL-cholesterol, triglycerides)	X	X		X
	Glucose metabolism (glucose, HbA1c)	X	X		X
	Clinical parameters (CRP, ASAT, ALAT, urea, creatinin, TSH, leukocytes)	X	X		X
Psychological measures	CDSS	X	X		X
	PANSS	X	X		X
	HoNOS	X	X		X
	MANSA	X	X		X
Lifestyle habits	Functional physical fitness	X	X		X
	(six-minute walk test)*				
	Daily physical activity (SQUASH)*	X	X		X
	Food frequency questionnaire (adapted to patient population)				
Cost-effectiveness	Dutch care consumption questionnaire*	X	X		X
	SF6D*	X	X		X
**Measurements on team level**					
General information	Age, gender, birth year, level of education, number of years working in psychiatry, function*	X	X		X
Process evaluation	Semi-structured interview team leader*	X	X	X**	X
	Semi-structured interview staff*	X	X	X**	X
	Semi-structured interview patients*	X	X	X**	X
	Observatory list*	X	X	X**	X
Staff questionnaire	Knowledge on diet and physical activity, attitude towards lifestyle changes in patients, self-efficacy in addressing lifestyle issues with patients*	X	X		X

*Measurement is not part of ROM screening. Additional measures are collected by research assistants.

**Measures are collected at intervention teams only.

Some measurements are not part of ROM and will be carried out by research assistants, mostly the lifestyle coaches. Research assistants will receive one day training to study protocols and procedures and to practice assessing the functional physical fitness in patients with the six-minute walk test, assessing the body fat percentage with the Bioelectrical impedance analysis, measuring height and weight, assessing food habits with a food questionnaire based on Dutch guidelines for a healthy diet which is adapted to this population, and questionnaires and interviews with patients and staff for process evaluation. All measurements will be taken on site or in a location that is familiar to the patient (e.g. patient’s own room, nurses’ office). Research assistants contact patients directly to set up an appointment or staff members act as intermediaries to facilitate setting up appointments. Appointments for interviews with staff members are scheduled by research assistants and staff members.

### Measurements on patient level

Patient measurements include cardiometabolic health, disease history, medication use, mental health, psychosocial functioning, quality of life, lifestyle habits, care consumption and general information (i.e. age, gender).

Cardiometabolic health. The physical measurements include waist circumference, height, weight, pulse and systolic and diastolic blood pressure. Patients visit a (hospital) laboratory that collects a blood sample, if possible in fasting state for levels of lipids (total cholesterol, LDL-cholesterol, HDL-cholesterol and triglycerides), glucose metabolism (glucose, HbA1c) and clinical parameters (i.e. CRP, ALAT, ASAT, urea, creatinine, TSH, leukocytes) and vitamin D status. Measurements are taken following standard ROM protocols. Waist circumference is measured in duplicate using a flexible nonstretching tape halfway between the iliac crest and lowest rib in standing position at the end of an expiration. Weight is measured by calibrated scales (Seca, model 813) in light clothing without shoes or jackets. Measurements for height will be available from multiple measurements of both ROM nurses and research assistants. The highest height will be used unless patients wear shoes, then the highest height without shoes is used. Pulse and systolic and diastolic blood pressure are measured after 5 minutes’ rest in sitting position, using a blood pressure monitor (BOSO medicus control). Body fat percentage is measured in standing position [23] by bioelectrical impedance analysis (BIA) in triplicate using a single-frequency bioimpedance analyzer (Model BIA 101, AKERN Srl, Italy) [24,25].

Mental health. During an interview, trained nurses administer the PANSS (Positive and Negative Syndrome Scale, [26]) and the CDSS (Calgarary Depression Scale for Schizophrenia, [27]). Prior to the interview, patients fill in the MANSA, a self-report questionnaire about patients’ Quality of Life [28] and uncertainties can be discussed during the interview. The HoNOS (Health of the Nations Outcome Scale, [29]) is an observation scale of psycho-social functioning and is scored by the case manager or team.

Lifestyle habits. Functional physical fitness is assessed by research assistants with a detailed protocol for the six-minute walk test [30], which contains standard phrases and time points for encouragement and has been validated in patients with schizophrenia [31]. The intraclass correlation coefficient was 0.96. Although a mild practice effect was detected for a three-day interval, this is unlikely to persist for a three–month interval. The test is conducted indoors. Patient staff is allowed to walk along with patients if necessary. Daily physical activity is assessed using the Dutch validated SQUASH questionnaire [32]. Nutritional habits are estimated using a semi-quantitative food frequency questionnaire with items based on a screening questionnaire for healthy eating habits of the Netherlands Nutrition Center according to the Dutch guidelines for a healthy diet [33] and adapted to this population. The questionnaire will be used to assess changes in dietary habits on food group level. It is not specifically validated in SMI patients and can and will not be used to derive quantitative estimates of total energy, macro- or micronutrient intake.

Cost-effectiveness parameters. Care consumption is estimated with the Dutch care consumption questionnaire [34], which is adapted to the context of the current study. Quality adjusted life years (QALYs) will be the primary outcome measure in the cost-effectiveness analysis. In order to estimate QALYs, utility scores will be derived from the SF12, using the SF6D algorithm [35,36].

### Measurements on team level

Measurements at team level include lifestyle knowledge and attitudes from staff, level of support of team managers, and process evaluation. Mental health care professionals are asked to fill in questionnaires for process evaluation and staff characteristics as potential determinants of successful intervention at baseline, and three and 12 months after start of the intervention.

Process evaluation. One research assistant visits all teams (both control and intervention) and will interview the team leader, staff and patients separately, using semi-structured interviews, at baseline, three months and 12 months to determine which lifestyle activities are initiated and sustained. These measurements are in addition to the monthly monitoring visits that have a more advisory character. The interviews contain questions on organisational aspects (e.g. is anyone in the team specifically responsible for the lifestyle activities and if yes state name) as well as on lifestyle-related activities. These activities will be reported in great detail (what is being organised, for how long, how often, how many participants from the housing facility participate, and more). Questions, translated from Dutch, are for example “How many times per week are physically intensive activities offered?”, “What have you changed in food supply?”, “What type of food workshops have you organised?” and “Are patients stimulated to do household chores?”. During these visits, the research assistant will screen kitchen cabinets, refrigerator and shared living rooms to determine the level of ‘obesogenic environment’ (e.g. fruit on the table, healthy products in store or products with reduced fat and energy in the cabinets and refrigerator, number of exercise activities written in the team’s calendar). The information is combined to establish adherence to the lifestyle plan and the degree and quality of implementation of the intervention.

Mental health professionals’ characteristics. Data on age, education and experience are collected at baseline. At baseline, and three and 12 months after the start of the intervention, at least three members of the team will be asked to fill in questionnaires to rate their knowledge on diet and physical activity, attitude towards lifestyle changes in patients, and self-efficacy in addressing lifestyle issues with patients (Staff questionnaire). The questionnaire is developed based on existing questionnaires from the Netherlands Nutrition Center to evaluate lifestyle knowledge. Questions on attitude and self-efficacy are based on the ACE-model, better known as the ASE-model. This model describes the relationship between a persons’ attitudes, social influences and self-efficacy, and his or her behaviour. Questions are adapted to fit the study design and patient group [37,38].

### Sample size

The primary objective in this study is to detect a difference in waist circumference with clinical significance. Sample size calculations show that to detect a significant change of −5% waist circumference [39] (alpha =0.05, power 0.90), 219 patients are needed in both intervention and control arm. Research in psychiatric patients usually shows a high drop-out rate. However, since in this project patients are living intramurally and most measurements are part of standard care, it is expected that the drop-out rate, once having signed an informed consent, will not exceed 10%. Therefore the target number of patients to include in both intervention and control arm is 240 (N = 219 + 10% drop-out). In both mental health organisations together, approximately 1000 eligible SMI patients live in residential or long-term clinical care facilities. Results from a pilot study show that two thirds of patients will successfully participate in the measurements which means that the two organisations will suffice to include the necessary 240 patients per arm. This number will also be sufficient to demonstrate for example a 4.7% reduction in plasma glucose. The clustered nature of the trial requires some extra thoughts on loss of power in multilevel analyses. However, as we a have a large number of clusters (13 clusters; see below) and a large number of patients per cluster (range from 44 to 130), the interdependency of observations will be limited. This may justify using individual patient rather than clustered sample size calculations [40].

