### Participants

All residential and long-term clinical care teams of two large mental health organisations in the North of the Netherlands, a catchment area of 1.2 million inhabitants, are invited to participate in the study (N = 30). One residential team exclusively serving patients suffering from Korsakov’s syndrome is excluded. Team leaders are informed by an invitation letter followed by a meeting to explain the study. Teams are visited by the project leader to explain the aims of the study and answer questions. Teams serve severe mentally ill patients, often with a diagnosis of schizophrenia or other psychotic disorder, most of whom have been living in residential facilities for at least 10 years. Caseload sizes vary from 20 to 65 patients per team. In the Netherlands, patients living in residential facilities live as independently as possible, with a team of professionals nearby. Patients are housed alone or in small groups in a community neighbourhood. Long-term clinical care facilities provide more intensive professional care and assistance in activities of daily living. Housing is provided in the sheltered and safe environment of the mental health care organisation.

All patients are invited to participate, as they are all at increased risk of unhealthy lifestyle habits due to their obesogenic living environment, and all patients are considered to have an increased cardiometabolic risk. Exclusion criteria are age below 18, pregnancy and being unable to perform physical activity tests (e.g. wheelchair user). Patients not taking part in the yearly routine outcome monitoring (ROM, see ‘outcomes’), that is used for this study to monitor intervention effects, will not be included in the analysis. In the mental health organisation Lentis (~50% recruitment area) only patients using antipsychotic medication are routinely monitored. Therefore, patients from Lentis not using antipsychotic medication are excluded.

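### The target of 240 per arm falls just short of 219 evaluable at the plan's own 10% drop-out ceiling, and the reason given for 10% partly conflicts with the description of the participants

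*Protocol article*

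**What the plan says.** The Sample size section of the protocol article gives the requirement as "alpha =0.05, power 0.90), 219 patients are needed in both intervention and control arm", for an effect described as "to detect a significant change of −5% waist circumference". It concedes that drop-out in psychiatric research is usually high, then makes an exception for this trial: "since in this project patients are living intramurally and most measurements are part of standard care, it is expected that the drop-out rate" will be low. The ceiling is set at 10%, counted after consent. From this it concludes that "the target number of patients to include in both intervention and control arm is 240 (N = 219 + 10% drop-out".

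The same section puts the eligible population at about 1000. It cites a pilot in which two thirds of patients took part successfully in the measurements, and concludes that the two organisations can supply 240 per arm.

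Two other sections bear on the rationale. Under Participants, patients in residential facilities live as independently as they can with a team close by: "Patients are housed alone or in small groups in a community neighbourhood". Only long-term clinical care is described as housed within the organisation itself. Under Outcomes, baseline and 12 months use the regular yearly routine outcome monitoring (ROM), whereas "an additional ROM screening will be carried out at three months", for which patients receive a small fee. Waist circumference is the primary outcome at both 3 and 12 months (Abstract and Objectives).

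**The concern.** Two things look wrong.

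The first is the inflation step. Adding 10% to the required number is not the same as enrolling enough to have that number left after a 10% loss. The target should return 219 at the ceiling the plan sets for itself, and it does not.

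The second is the argument for 10%. The section departs from what it calls the usual experience in the field and gives two reasons. Intramural living does not fit the article's own account of its residential patients, who are the population named in the trial's aim. The reliance on standard care is weaker at 3 months, because that round is added for the study. No retention figure is cited in support.

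At stake is whether the stated target delivers the evaluable number on which the power statement rests, and whether a reader can trust the small allowance for loss.

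**Working it through.** **Inputs**
- Required evaluable number: 219 per arm; alpha 0.05; power 0.90; drop-out at most 10% after consent; target 240 per arm; about 1000 eligible; pilot participation two thirds (all from Sample size).
- Assumptions: two-sided alpha (the section does not state sidedness), a normal approximation, individual patients as the unit (as the section itself assumes), and equal arms.

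**The plan's own figure**
- 219 × 1.10 = 240.9, given as 240. The figure is reproduced by adding 10% and rounding down; rounding up would give 241.
- The 219 itself cannot be checked, because no standard deviation is given. Back-solving 219 per arm for a 5% difference gives a standardised effect of (1.96 + 1.2815) × √(2/219) = 0.310, so a standard deviation of 5/0.310, about 16.1% of mean waist.

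**Does 240 deliver 219?**
- Evaluable at 10% loss: 240 × 0.90 = 216, which is 3 short.
- Largest loss that 240 can absorb: 1 − 219/240 = 0.0875, or 8.75%.
- Enrolment needed at 10% loss: 219/(1 − 0.10) = 243.3, so 244.

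**Power at 216 per arm**
- Scaling from 0.90 at 219: Φ(3.2415 × √(216/219) − 1.96) = Φ(1.259) = 0.896. The standard deviation cancels in this step.

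**What the invited pool can supply**
- 1000 × 2/3 = 667, or about 333 per arm.
- Evaluable at 10% loss: 333 × 0.90 = about 300.
- Largest loss that still leaves 219: 1 − 219/333.3 = 0.343, or about 34%.

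**The rationale against the other sections**

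| Reason given under Sample size | What the article says elsewhere | Result |
|---|---|---|
| Patients live intramurally | Participants: true of long-term clinical care; residential patients live in the community with a team nearby | Contradicted for the residential group; its share of the 1000 is not given |
| Most measurements are standard care | Outcomes: baseline and 12 months are routine ROM, 3 months is additional | True as a count (two of three rounds), but it does not cover the 3-month primary time point |

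**The case against.** The strongest reply is that this is rounding. The section shows its rule openly, 240 follows from it, and four patients per arm move power by less than half a percentage point. That is right about the size. It does not make 240 return 219 at the stated ceiling.

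The reply on retention is also strong. Residential patients have staff nearby and most have lived in such facilities for ten years or more. Nurses visit them, measurements are taken on site or somewhere familiar, and the 3-month round is run by the same ROM nurses with a fee. The claim is that most measurements are standard care, not all, and that remains true. A missed 3-month visit need not remove a patient, since the analysis is a longitudinal mixed model with multiple imputation planned under missing at random. So community housing and one extra visit do not show that loss will exceed 10%.

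A reader might go further and treat the pilot's two thirds as a sign that a third of enrolled patients will be lost. The document does not support this. The pilot figure describes participation among all patients, while the 10% applies after consent. Using it for both would count the same patients twice. No other figure in the article points to a specific loss above 10%.

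A reader might also infer that recruitment could close at 240 with too few evaluable patients. No such stopping rule is stated. All patients of the invited teams are approached, and the expected yield is well above 240.

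What survives is the mismatch between 240 and 219, and a rationale that the article partly contradicts without citing retention data.

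**Conclusion.** The point holds in a narrow form. At the plan's own 10% ceiling, 240 per arm yields 216 evaluable patients, 3 below the requirement, with power about 0.896 instead of 0.90. The error is real but small. That power figure takes the 219 as given, ignores clustering as the section does, and assumes a two-sided test.

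The intramural rationale conflicts with the Participants section for residential patients, and the standard-care rationale does not extend to the 3-month primary visit. This weakens the support for 10% without showing it to be wrong. It would go too far to call the target unsupported: only the drop-out step, 21 patients per arm (240 − 219), is affected, and the invited pool has room for far greater loss. The pool figure rests on the article's approximate 1000, on the pilot's two thirds holding in the trial, and on a roughly equal split between arms.

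**What to change.** In the Sample size section:

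1. Replace 240 with 219/(1 − 0.10) = 244 per arm, or keep 240 and state that it yields 216 evaluable at 10% loss, with power about 0.896.
2. Reconcile the statement about intramural living with the Participants section, for example by limiting it to long-term clinical care and giving the retention argument for residential patients in its own terms (staff nearby, nurses visiting, measurement on site).
3. Note that the 3-month round is outside routine care, so the standard-care argument covers baseline and 12 months only. Cite retention data for the 10% if any exist; otherwise label it an assumption.
4. Report the evaluable number expected from the invited pool: about 333 per arm before loss, about 300 at 10% loss, and still 219 at about 34%.

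The cost is a few sentences and one number. No teams, visits or procedures are added, because every eligible patient is already invited.

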### Randomisation

After recruitment, teams are randomised to intervention or control condition. To ensure comparability of teams in the intervention and control arm, clusters of comparable teams are made based on health care organisation, level of intensity of care (long-term residential or long-term clinical care), caseload size and location (urban or rural). Each cluster consists of two comparable teams in terms of these variables; one cluster contains five comparable teams. Of each cluster, the teams are randomly allocated to one of the two conditions by a computerised random number generator. A research nurse not involved in the study reveals the results of the allocation. All participating teams are randomised simultaneously making allocation sequence concealment unnecessary.

Blinding of teams and patients to the allocation condition is not possible due to the nature of the intervention. Research nurses assessing the outcomes in the ROM screenings are blinded to the intervention allocation. The research assistants taking the six-minute walk test, body fat test and lifestyle questionnaires in patients and staff are not blinded to the intervention at the baseline and 3 months measurements. Outcome measures at 12 months after baseline are however carried out by different research assistants that are not informed of the allocation status of the teams and patients. All post-intervention measures at 12 months after start of the intervention will thus be obtained blinded.

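### The 219 per arm comes from an individual-patient calculation in a team-randomised trial, and the reason given for ignoring clustering runs backwards, so the stated 0.90 power is unsupported

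*Protocol article*

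**What the plan says.** The Sample size section of the protocol article aims "to detect a significant change of −5% waist circumference" and gives the result as ("alpha =0.05, power 0.90), 219 patients are needed in both intervention and control arm". The recruitment target follows: "the target number of patients to include in both intervention and control arm is 240 (N = 219 + 10% drop-out"). No SD, baseline mean, baseline correlation, sidedness, ICC or design effect is given.

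The section then raises the loss of power in multilevel analyses and sets it aside. It first points to "a large number of clusters (13 clusters; see below"). Next it brings in cluster size and draws its inference: "a large number of patients per cluster (range from 44 to 130), the interdependency of observations will be limited". It concludes: "This may justify using individual patient rather than clustered sample size calculations", citing a source.

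Three other places bear on this:

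- **Randomisation:** teams are allocated to the two conditions within each cluster. "Each cluster consists of two comparable teams in terms of these variables; one cluster contains five comparable teams".
- **Participants:** "Caseload sizes vary from 20 to 65 patients per team".
- **Statistical methods:** the primary analysis is a multilevel linear mixed model that accounts for clustering by team and adjusts for baseline scores.

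**The concern.** The trial is analysed as a cluster trial but sized as an individually randomised one. The analysis will carry a clustering cost that the sample size sets to zero.

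The written reason does not justify this. The number of patients per cluster does not reduce the correlation between patients in the same team. For a given total and a given ICC, larger clusters cost more power. Nor is zero correlation a natural default here: patients of a team share staff and food supply, and the intervention works by changing that shared environment.

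The unit is also mislabelled. The 13 clusters each contain teams from both arms, so they are strata for the randomisation and not the randomised units.

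What is at stake is how a result near the null is read. A reader who takes 0.90 at face value would believe a 5% difference had been given a 90% chance of detection, and nothing in the section shows that.

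**Working it through.** **Inputs from the protocol.** Alpha 0.05, power 0.90, 219 per arm, 240 per arm with drop-out, about 1000 eligible patients of whom two thirds are expected to take part (Sample size); matching sets of teams (Randomisation); caseloads of 20 to 65 (Participants).

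**Assumed.** A two-sided test; ICC of 0.01, 0.03 and 0.05; equal team sizes; normal approximation.

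**1. The plan's own figure.** With no SD stated, 219 cannot be reproduced independently and has to be back-solved:

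d = (1.960 + 1.282) × √(2/219) = 0.310

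For a 5-point difference this implies an SD of 5/0.310 = 16.1 percentage points. A one-sided test would imply d = 0.280 and an SD of 17.9. Either way, 219 is consistent with the plain two-sample formula with a design effect of 1.

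**2. The unit.** Thirteen matching sets, 12 of two teams and one of five, give 12 × 2 + 5 = 29 teams. The Discussion also gives 29 eligible teams. A range reaching 130 patients cannot describe single teams with at most 65; two teams of 65 make 130.

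**3. Direction of the argument.** Design effect DE = 1 + (m − 1) × ICC. At an assumed ICC of 0.02:

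- m = 15.1: DE = 1.28
- m = 44: 1 + 43 × 0.02 = 1.86
- m = 130: 1 + 129 × 0.02 = 3.58

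**4. Power without baseline credit.** Power = Φ(d × √(n/(2 × DE)) − 1.960), with n per arm and m = 2n/29.

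| Patients analysed | m | ICC 0.01: DE, power | ICC 0.03: DE, power | ICC 0.05: DE, power |
|---|---|---|---|---|
| 438 (219 per arm) | 15.1 | 1.14, 0.86 | 1.42, 0.78 | 1.71, 0.70 |
| 480 (240 per arm, no drop-out) | 16.6 | 1.16, 0.88 | 1.47, 0.80 | 1.78, 0.72 |
| 667 (all expected participants) | 23.0 | 1.22, 0.95 | 1.66, 0.87 | 2.10, 0.79 |

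At 438 patients, a t reference on 27 team-level degrees of freedom gives 0.833, 0.745 and 0.668.

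**5. Baseline adjustment.** If the implied SD is cross-sectional, adjusting for a baseline value with correlation r multiplies the variance by 1 − r². Power returns to 0.90 at 219 per arm when DE × (1 − r²) = 1, that is r = √(1 − 1/DE):

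- ICC 0.01: r ≈ 0.35
- ICC 0.03: r ≈ 0.55
- ICC 0.05: r ≈ 0.64

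At an assumed r of 0.8 and ICC 0.05, DE × (1 − r²) = 1.71 × 0.36 = 0.61. Power for a 5% difference is then about 0.98, and the difference detectable with 90% power is 5 × √0.61 ≈ 3.9%.

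**6. Does the miscount matter?** Treating 13 as the number of randomised units (m = 438/13 = 33.7) would give power of 0.80 at ICC 0.01 and 0.51 at ICC 0.05. With 29 teams the figures are 0.86 and 0.70. Correcting the count helps the authors.

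**The case against.** A reader might infer that the trial is underpowered, or that 0.90 is out of reach for this design. The protocol does not support that. Statistical methods commits to baseline adjustment, and step 5 shows that a moderate baseline correlation would restore 0.90 if the SD behind 219 is cross-sectional. The section speaks of a change in waist circumference, however. If the SD was already one of change, part of that credit has been spent. The document does not say which, so neither adequate power nor a shortfall can be established. About 667 participants are also expected against a target of 480, which gives above 0.90 at ICC 0.01 even without baseline credit, though not at 0.03 or 0.05.

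A reader might also blame the wrong cluster count for the shortfall, or think the analysis invalid. Neither holds. The miscount is a labelling error that works against the authors, the Randomisation section openly defines the sets, and the planned model accounts for team clustering.

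It can fairly be said that the text only claims its argument may justify the shortcut, and that it cites a source not available here. Yet the targets of 219 and 240 rest on that shortcut, and the reasoning as printed is wrong for team-randomised data whatever the source says. A fuller document could supply an ICC, but it could not make this reason correct.

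Two side matters carry no weight. On drop-out, 240 × 0.9 = 216 against 219, which gives a power of 0.896. Whether 44 to 130 counts eligible patients or participants is a matter of inference.

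**Conclusion.** The point stands as a defect in the stated justification. The sample-size section uses an individual-patient calculation for a team-randomised trial, and its reason for doing so has the effect of cluster size the wrong way round. On the calculation as written, 0.90 at 219 per arm holds only at ICC = 0.

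Confidence in the faulty reasoning is high. The size of the loss is much less certain: the ICC range, two-sidedness and equal team sizes are assumptions, the SD is back-solved, and the power figures in step 4 give no credit for baseline adjustment. The proper conclusion is that the stated power is unsupported, not that the design lacks it. The 4.7% glucose claim rests on the same number and shares the problem.

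**What to change.** In the Sample size section:

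- Delete the argument that cluster size limits interdependency.
- Name the 29 teams as the clusters, and call the 13 groupings matching sets or strata here and under Randomisation.
- State the SD behind 219, the sidedness of the test, and whether the SD is cross-sectional, of change, or baseline-adjusted.
- Restate power, or the detectable waist difference, for 480 and for the expected 667 patients over a stated ICC range such as 0.01 to 0.05, on the basis of the baseline-adjusted analysis already planned. If baseline correlation is credited, give the value assumed.
- Restate the 4.7% glucose claim on the same basis.

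The cost is a rewording and a short recalculation. The stated power may come out less favourable. No change in recruitment, design or analysis is asked for.
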